## 6.2 Pooling data for analyses

First, the appropriateness of a pooled analysis in subjects who are randomized individually or by cluster will be examined.

In this analysis, study participants assigned by individual randomization and cluster randomization will be analyzed. Cluster randomization in the study will be as follows: Communities or healthcare providers are a randomization unit; explanation and consent are given individually; interventional effect is on an individual basis; and subjects with a diagnosis of breast cancer are those with objective data from a medical examination.

For the estimation of the primary endpoints, generalized estimating equation (GEE) with a compound symmetry structure as a working correlation matrix will be used. Analyses including only subjects who are randomized individually or by cluster will be performed, and it will be reviewed that the point estimates of the primary endpoints are similar. Furthermore, a model including the randomized groups as well as an interaction between the randomization methods (either individual or cluster) and randomized groups as an explanatory variable will be applied to subjects pooled from the two analyses, and it will be evaluated that the interaction effect is not statistically significant. If there is no interaction, a pooled analysis including subjects who are randomized individually and by cluster will be carried out.

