## 7. Statistical Analyses

### 7.1 Comparison of characteristics of baseline demographic variables and the distributions of baseline factors

Baseline demographic variables will be age at the time of enrollment, history of breast cancer screening (presence or absence, date of screening and methods), the age of first menstruation, menstruation status, number of pregnancies, frequency of childbearing, age at the first delivery, feeding history, family history of breast cancer, history of breast surgery, and history of mammary gland disease.

351 Age at the time of enrollment and time (month) from the previous screening. History of screening, menstruation  
 352 status, feeding history, family history, history of breast surgery, and history of mammary gland disease. Time  
 353 (month) from the previous screening, which is a continuous variable, will be categorized. The age of first  
 354 menstruation, number of pregnancies, frequency of childbearing, age at the first delivery, and number of  
 355 first-degree relatives with breast cancer will be categorized in accordance with the Gail model for performing an  
 356 international comparison.

357 For characteristics of baseline demographic variables, descriptive statistics will be calculated to describe the data.  
 358 Continuous variables will be summarized with a number, mean, standard deviation, range and mode. Categorical  
 359 data will be presented as percentages. For methods of comparisons of the distributions of baseline factors,  
 360 differences in categorical data will be assessed by Fisher’s exact test and the Chi-square test, and differences in  
 361 continuous data by the Mann-Whitney’s U-test. All tests will be two-sided.

362 7.2 Analyses of a detection rate, sensitivity and specificity of the first screening and calculation methods  
 363 for 95% confidence intervals (CIs)

364 7.2.1 Definitions and calculation formulas

Table 2. Definitions and calculation formulas of a detection rate, sensitivity and specificity of the first screening

|                                            |                                                                                                              |                                                                              |

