|                                                                              | Mean, standard deviation, median | Significant digits will be rounded to the nearest tenth and displayed up to one digit.                                                                                                                                                                      |
|                                                                              | Minimum                          | The same number of figures as significant digits will be displayed.                                                                                                                                                                                         |
|                                                                              | Maximum                          | The same number of figures as significant digits will be displayed.                                                                                                                                                                                         |
|                                                                              | Interquartile range              | The same number of figures as significant digits will be displayed.                                                                                                                                                                                         |
| Test/ estimation                                                             | P value                          | Rules specified by a journal, to which results will be submitted, will be followed. The value will be rounded off to the nearest thousandth and displayed up to three decimal places. However, when it is less than 0.001, it will be displayed as < 0.001. |
|                                                                              | Significance level               | A two-sided test will be performed with a significance level of 5%. If other values are used for significance levels, they will be mentioned at each time. The confidence coefficient of interval estimation will be two-side 95%.                          |

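### The baseline tests in SAP 7.1 ignore cluster randomisation, so their p-values are too small wherever cluster-randomised women are included and baseline factors correlate within clusters

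*Combined protocol and SAP*

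**What the plan says.** SAP 7.1 begins with description: "For characteristics of baseline demographic variables, descriptive statistics will be calculated to describe the data". It then adds tests. Categorical factors are compared by Fisher's "exact test and the Chi-square test, and differences in" "continuous data by the Mann-Whitney’s U-test. All tests will be two-sided". SAP 8 sets the two-sided level at 5%. Section 7.1 names no adjustment for clustering, no standardised difference and no split by randomisation method. It does not specify a table layout.

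SAP 6.2 says who is analysed: "In this analysis, study participants assigned by individual randomization and cluster randomization will be analyzed". On the cluster part it states: "Communities or healthcare providers are a randomization unit; explanation and consent are given individually". SAP 6.2 and 7.2.2 use GEE with a compound symmetry working correlation for the primary endpoints, and 7.2.2 adds a robust variance. Neither section extends this to the baseline comparison.

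On recruitment, Protocol 16.1 items (1) and (2) have the institutional data center invite women, check eligibility and take consent. Protocol 16.2 item (5) has the Central Data Center randomise organisations that use the cluster design and report the result to that same institutional data center. Sites that randomise individually instead receive sealed, numbered envelopes (16.2 item (4)).

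**The concern.** The SAP treats women in the same community or provider as correlated when it analyses the endpoints, and as independent when it compares baseline factors. Age, screening history, childbearing history and similar factors may well differ between communities and providers. If they do, a difference between arms in the cluster part is more variable than the three tests assume, and p-values below 0.05 occur too often.

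This matters because a baseline comparison has a real purpose in the cluster part. Consent is individual, and the allocation is reported to the body that recruits. Staff could therefore know the arm when they approach a woman, and recruitment could differ between arms. The documents do not state the order of allocation and consent, so this is a possibility and not a finding. A reader who sees a significant baseline factor would want to know whether it reflects recruitment or only the spread between clusters, and the planned p-value cannot say which.

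**Working it through.** The plan gives no figure for the baseline tests, so there is none to reproduce. It also gives no ICC, no cluster size and no number of cluster-randomised women. These inputs are assumed below and shown as ranges.

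**Step 1. False-positive rate when every woman is in a cluster.** With cluster size m, the design effect is DE = 1 + (m − 1) × ICC. A test that ignores clustering at a nominal two-sided 5% rejects with probability 2 × [1 − Φ(1.96/√DE)]. Example: m = 500 and ICC = 0.01 give DE = 1 + 499 × 0.01 = 5.99, 1.96/√5.99 = 0.80, and a rate of 42%.

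**Step 2. Mixed sample.** If a share f of the women is in clusters, DE becomes 1 + f × (DE − 1). Example: f = 0.25 with m = 500 and ICC = 0.01 gives 1 + 0.25 × 4.99 = 2.25, and a rate of 19%.

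| Cluster size m | ICC | All in clusters | 25% in clusters | 10% in clusters |
|---|---|---|---|---|
| 50 | 0.001 | 5.6% | 5.1% | 5.1% |
| 50 | 0.01 | 10.8% | 6.4% | 5.6% |
| 50 | 0.05 | 29% | 12% | 7.9% |
| 500 | 0.001 | 11% | 6.5% | 5.6% |
| 500 | 0.01 | 42% | 19% | 11% |
| 500 | 0.05 | 70% | 47% | 29% |
| 1,905 | 0.001 | 25% | 11% | 7.2% |
| 1,905 | 0.01 | 66% | 41% | 25% |
| 1,905 | 0.05 | 84% | 69% | 55% |

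The largest m is 80,000/42: the planned enrolment in SAP 3.1 divided by the organisations in SAP 2.2, as if a whole organisation were one cluster. The formula describes the chi-square test. Fisher's exact test nearly coincides with it at these numbers, and the Mann-Whitney test is inflated in the same way by correlation of the ranks.

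**Step 3. What a significant result tells the reader.** Simulation of a binary factor at 30% prevalence, 20 clusters per arm of 500 women, beta-binomial, 4,000 runs per setting. The comparison is a t-test on cluster proportions.

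| ICC | Unadjusted, no imbalance | Unadjusted, true 3-point imbalance | Cluster-level, no imbalance | Cluster-level, true 3-point imbalance |
|---|---|---|---|---|
| 0.001 | 11% | 98% | 5.2% | 95% |
| 0.01 | 43% | 86% | 5.4% | 45% |
| 0.05 | 70% | 79% | 5.3% | 13% |

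At ICC 0.01 an unadjusted significant result is about twice as likely with a true imbalance as without (86/43 = 2.0). At ICC 0.05 the ratio is 79/70 = 1.1. The cluster-level test gives 45.1/5.4 = 8.4 and 13.4/5.3 = 2.5. The unadjusted test still reacts to a real shift. What it loses is specificity.

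**Step 4. Would a fixed flag on the standardised difference be safer?** With k large clusters per arm and no imbalance, the standardised difference has a standard deviation of about √(2 × ICC/k). For 20 clusters in total (k = 10) and ICC 0.03 this is √0.006 = 0.077, so an absolute value above 0.1 occurs in about 20% of comparisons. With 40 clusters it is √0.003 = 0.055, or about 7%. At ICC 0.005 it is 1% or less. A robust GEE test without correction behaves roughly like a t-test with 2k − 2 degrees of freedom and critical value 1.96 × √((k − 1)/k). That rejects about 8% with 20 clusters and 6% with 40.

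**The case against.** The strongest reply is that little depends on these p-values. Section 7.1 plans descriptive summaries as well, and no decision rule, covariate choice or conclusion follows from a baseline test. The GEE for the primary endpoints allows for clustering. SAP 6.2 also requires separate individual-only and cluster-only estimates with an interaction test, and SAP 6.4.1 checks compliance with randomisation and looks for consent dated after screening. All of this stands and limits the point to how the table is read. None of it replaces a baseline comparison in the cluster part or makes the stated tests valid there.

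A reader might infer more than the documents support:

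- **That the tests cannot show a real recruitment imbalance.** They over-reject, so they do not hide a shift: 79% to 98% of runs in Step 3 flagged a true 3-point difference. The percentages by arm would also still show its size.
- **That significant results would mostly reflect clustering or chance.** The excess runs from negligible to dominant over the assumed inputs, and nothing in the documents fixes a place in that range.
- **That the tests also fail in individually randomised women because the trial is large.** With no imbalance, a valid test rejects 5% of the time at any sample size. The 43% chance of at least one significant result among 11 factors (1 − 0.95^11) is ordinary multiplicity. It also treats as independent several factors that are clearly related, such as pregnancies, births and feeding history. Removing the tests in this group is a matter of preference.
- **That SAP 7.1 judges comparability by p-value in one pooled table.** The text says neither. It is silent on layout and on any inference from the tests.

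**Conclusion.** The point holds as a limited one. SAP 7.1 specifies tests that assume independence for a set that includes cluster-randomised women, while SAP 7.2.2 allows for clustering only for the primary endpoints. The direction of the error is certain for any positive ICC: the p-values are too small. Its size is not known. Under the assumed inputs the false-positive rate runs from about 5% (m = 50, ICC 0.001, a tenth or a quarter of women in clusters) to 70% at m = 500 and ICC 0.05 with all women in clusters, and 84% if whole organisations were clusters.

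The consequence is for reading the baseline table and does not reach the primary result. The extent in the breast-density analysis that this SAP version describes is also unknown: SAP 5.5 draws those cases from the Miyagi screening center, and the documents do not say how those women were randomised. If all were individually randomised, the problem would be absent there.

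**What to change.** In SAP 7.1:

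1. Present each baseline factor by arm separately for individually and cluster-randomised women, with standardised differences. Treat these as descriptive. Set no fixed 0.1 threshold in the cluster part, because Step 4 shows that it can be crossed by chance in about a fifth of comparisons.
2. Do not use Fisher's exact, chi-square or Mann-Whitney tests for any comparison that includes cluster-randomised women. They may stay for the individually randomised women if the team wants them.
3. If a p-value is wanted for the cluster part, take it from a cluster-level test, or from a GEE with the randomised unit as the cluster and a small-sample correction.
4. State how the women in the Miyagi density analysis were randomised, so that readers know whether this applies to them.

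The cost is SAP wording, one split table and the loss of the simple p-value column for pooled or cluster-randomised women. No new data are needed.

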### 2.2 Study design

The following two groups will be set to evaluate the efficacy of breast cancer screening using ultrasonography in women aged 40 to 49 years:

- 1) Group using ultrasonography in combination (intervention group)  
(mammography + ultrasonography, or mammography + CBE + ultrasonography)
- 2) Group without ultrasonography (non-intervention group)  
(mammography alone, or mammography + CBE).

For scientific evidence, designs such as an individual randomized control study, cluster randomized control study, and non-randomized control study can be assumed. From the viewpoint of performing a high-quality study, an individual randomized control study is the most appropriate followed by a cluster randomized control study. If random allocation cannot be done, a non-randomized control study has to be chosen, and a method to compare with the non-intervention group without randomization has to be considered. A total of 42 organizations in 23 prefectures in Japan will participate in the study.

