|--------------------------------------------|--------------------------------------------------------------------------------------------------------------|------------------------------------------------------------------------------|
| Detection rate of screening, %
(95% CI) | The number of cancers with a positive initial interpretation among 1,000 screening examinations.             |                                                                              |
| Sensitivity, %
(95% CI)                 | $\text{Sensitivity} = \frac{[5]\text{TP}+[7]\text{TP}}{[5]\text{TP}+[7]\text{TP}+[1]\text{FN}+[3]\text{FN}}$ | (Number of true positive assessments) / (Number of all positive assessments) |
| Specificity, %
(95% CI)                 | $\text{Specificity} = \frac{\text{TN}}{\text{TN}+\text{FP}}$                                                 | (Number of true negative assessments) / (Number of all negative assessments) |

365 The 95% CIs will be calculated using the binomial distribution method.

366 At the statistical analysis/ data monitoring committee meeting held on October 28, 2013, consensus was reached  
 367 that subjects having an unknown status would be excluded from the analyses of sensitivity and specificity.

368 7.2.2 Method of the primary analysis taking account of correlations within the cluster

369 All “screen-detected cancer,” “interval cancer” and “subjects without cancer” at the first screening to be used for  
 370 calculating sensitivity/ specificity, the primary endpoints, are binary outcomes. As an analysis method for  
 371 estimating the primary endpoints in the two groups, GEE taking account of correlations within the cluster will be  
 372 used. For estimation of the parameters, robust variance estimator with a compound symmetry structure as a  
 373 working correlation matrix will be employed.

374

375     **8. Statistical Analysis Rules**

| Item                                                                         |                                  | Display digit                                                                                                                                                                                                                                               |

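### SAP 7.2.1 prescribes binomial 95% CIs although cluster-randomised women are pooled and GEE is planned for the same endpoints; the SAP does not say which CIs are reported

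*Combined protocol and SAP*

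**What the plan says.** Four places in the SAP bear on this.

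- **7.2.1** gives the formulas for detection rate, sensitivity and specificity and marks each for a 95% CI. The instruction that follows is "The 95% CIs will be calculated using the binomial distribution method". It is not limited to descriptive use or to individually randomised women.
- **7.2.2**, the next subsection, is headed "Method of the primary analysis taking account of correlations within the cluster". For "estimating the primary endpoints in the two groups, GEE taking account of correlations within the cluster will be" used, with a "robust variance estimator with a compound symmetry structure as a" working correlation matrix. Its opening sentence names sensitivity and specificity but not detection rate.
- **6.2** states that "study participants assigned by individual randomization and cluster randomization will be analyzed". It also says: "For the estimation of the primary endpoints, generalized estimating equation (GEE) with a compound symmetry structure as a working correlation matrix will be used". Pooling depends on similar point estimates and a non-significant interaction between randomisation method and group. Separate individual-only and cluster-only analyses are planned as well.
- **8** (display rules) lists a 95% CI for the rate beside sensitivity, specificity and detection rate, and a separate CI row under tests and estimation.

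No section says which method supplies the published per-arm intervals, or how the interval for the between-group difference is formed.

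**The concern.** A binomial variance is valid when women's outcomes are independent. In the cluster-randomised part, communities or healthcare providers are allocated as a whole, so women in one cluster share an allocation and may also share readers and recall habits. The protocol gives reasons to expect this. Category judgements are made by each facility's readers (6.1.1, 6.1.2), and clinical breast examination is offered at some facilities and not at others (6.3). False-positive rates, and hence specificity, could well vary between clusters.

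At stake is the stated precision of the primary endpoints. A programmer who follows 7.2.1 literally produces per-arm intervals that ignore clustering, beside a GEE that allows for it. Readers tend to compare arms through their intervals, so the choice should not be left until results are known.

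**Working it through.** **1. The plan's own figure.** SAP 2.5 plans on sensitivities of 45/63 and 54/63, two-sided 5% and 80% power. With pooled variance and no continuity correction,

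n = [z₀.₉₇₅·√(2p̄(1−p̄)) + z₀.₈₀·√(p₁(1−p₁)+p₂(1−p₂))]² / (p₂−p₁)²

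- p̄ = 0.7857 and p₂−p₁ = 0.1429.
- n = (1.960×0.5803 + 0.8416×0.5714)² / 0.02041 = 128.3, so 129 cancers per group, against 130 stated.
- Women needed: 130 / (63/20,587) = 42,481 per group, against 42,500 stated.

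The figure reproduces under independence, with no design effect. That is a separate matter from the CI method, but it means no clustering parameter can be recovered from the sample size.

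**2. What a corrected interval would need.** The ICC, the number of clusters, their size and the cluster-randomised share are all absent, so no single corrected interval can be computed. What follows is an illustration.

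**3. Illustrative cluster size.** SAP 3.1 plans 80,000 women, and SAP 2.2 says "A total of 42 organizations in 23 prefectures in Japan will participate in the study".

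- Women per organisation: 80,000/42 = 1,905.
- Cancers per organisation: 1,905 × 63/20,587 = 5.8.

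Assumption: each organisation is one cluster and every woman is cluster-randomised.

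**4. Design effect.** DE = 1 + (m−1)·ICC. The correct interval is √DE times the binomial width. Approximate coverage of a nominal 95% binomial interval is 2Φ(1.96/√DE)−1. The ICC values are assumed.

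| Endpoint | m | ICC | DE | Width factor | Coverage |
|---|---|---|---|---|---|
| Sensitivity | 5.8 | 0.01 | 1.05 | 1.02 | 94.4% |
| Sensitivity | 5.8 | 0.05 | 1.24 | 1.11 | 92% |
| Specificity | 1,905 | 0.0001 | 1.19 | 1.09 | 93% |
| Specificity | 1,905 | 0.001 | 2.90 | 1.70 | 75% |
| Specificity | 1,905 | 0.01 | 20.0 | 4.48 | 34% |

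For specificity, m is all women in the organisation; removing the 5.8 cancers changes nothing material. Detection rate also has all screened women as its denominator, but its ICC may differ, so the specificity results should not be carried over to it.

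**5. Only a share f cluster-randomised.** The average design effect is roughly 1 − f + f·DE. For specificity at ICC 0.001:

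- f = 0.5: 0.5 + 0.5×2.90 = 1.95, width factor 1.40.
- f = 0.2: 0.8 + 0.2×2.90 = 1.38, width factor 1.18.

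For sensitivity at ICC 0.05, f = 0.5 gives 0.5 + 0.5×1.24 = 1.12, width factor 1.06. At ICC 0 or f = 0 there is no effect.

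**The case against.** The strongest reply is that the SAP already handles clustering. SAP 2.4.1 defines the primary endpoints as differences between groups. The binomial sentence sits under formulas for single proportions, and 7.2.2 then names GEE with a robust variance as the primary analysis. Section 8 lists the interval for a rate apart from the interval under tests and estimation. On this reading, binomial intervals describe each arm and GEE carries the comparison.

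That reading is coherent, and it rules out a stronger one. A reader might infer that the SAP fixes its primary inference as binomial and so contradicts its own GEE; the documents do not support that. But the SAP never states the benign reading either, and it does not rescue the per-arm intervals, which would still ignore clustering.

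Three further replies:

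- **Pooling is conditional.** True, but the interaction test asks whether the effect differs by randomisation method. Passing it says nothing about the ICC, and the planned cluster-only analysis has the problem undiluted.
- **The breast-density analysis uses Miyagi women only (5.5).** The mode of randomisation there is not stated, so the point may not touch that analysis.
- **The 42 organisations are not a count of clusters.** This stands. A reader might infer that the robust variance must have a small-sample correction, but one organisation may hold several clusters, or none if it randomised individually. Even with 40 degrees of freedom, t is 2.02 against 1.96, about 3% wider.

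**Conclusion.** Wrong as written, moderate severity. Section 7.2.1 prescribes an interval unsuited to cluster-randomised data, and the SAP does not reconcile it with the GEE of 6.2 and 7.2.2 or say which interval is reported.

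It would go too far to say that the reported intervals *are* too narrow. That needs three things the documents do not establish: an ICC above 0, a material cluster-randomised share, and the binomial intervals being the ones published. If all three hold, the direction is certain and the size depends on the endpoint. Sensitivity, which set the sample size, loses little because each cluster holds few cancers. Specificity could lose a great deal because each cluster may hold many women. The figures above are upper-end illustrations as regards the cluster-randomised share, since they set it at 100%. They also depend on the assumed ICCs and on equating organisations with clusters; the true clusters may be smaller or larger.

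**What to change.** Replace the sentence in SAP 7.2.1 with:

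> *Whenever cluster-randomised women are included, the reported 95% CIs for detection rate, sensitivity and specificity (per arm and between-group difference) are taken from the GEE with robust variance of 7.2.2. Binomial CIs are descriptive only, or are used for analyses restricted to individually randomised women.*

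In 7.2.2, name detection rate explicitly and state the cluster variable, including its value for individually randomised women. This choice matters. If the unit of randomisation is used, each such woman is her own cluster, and for that part the robust variance is close to the binomial one, leaving variation between facilities unaddressed. If the organisation is used, that variation is allowed for. The SAP should declare one choice before analysis.

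A small-sample correction to the robust variance is optional and should be decided from the actual number of clusters.

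The cost is a few sentences and a change to the source of the intervals in the SAS programs. No new data are needed. The downside is that the CIs may be wider, chiefly for specificity.

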## 2.5 Sample size

### Primary endpoints:

The primary endpoints are defined as differences in sensitivity/ specificity and a detection rate of the first breast cancer screening between the intervention group and non-intervention group as previously mentioned. The sample size was calculated based on a previous study comparing sensitivity between screening with CBE alone and mammography in combination with CBE.

In this study that was used for understanding interval cancer (cancer identified in screened individuals without abnormality during a period between the screening and the next screening) in population-based cancer registry data in Miyagi Prefecture, the sensitivity of breast cancer screening using mammography in combination with CBE was superior to that of CBE alone in all age groups. However, the sensitivity was 71.4% for the age of 40 to 49 years, 85.8% for the age of 50 to 59 years, and 87.2% for the age of 60 to 69 years; thus, it was lowest for the 40's. Of 20,587 subjects aged 40 to 49 years, breast cancer occurred in 63 subjects during two years after screening including screen-detected breast cancer. Of these, screen-detected breast cancer was in 45 subjects, and interval cancer was in 18 subjects (sensitivity:  $45/63 = 71.4\%$ ).

Furthermore, assuming that a combination with ultrasonography would increase the number of subjects with screen-detected cancer and that the incidence of interval cancer would be decreased by half (decrease from 18 to 9

subjects), sensitivity in the ultrasonography combined group would be 86% (54/63). A total of 130 subjects with breast cancer would be necessary for demonstrating this increase in sensitivity with a two-sided significance level of 5% at a power of 80%. When it was converted to the number of subjects undergoing screening, a sample size of 42,500 subjects per group was estimated.

Secondary endpoint:

The secondary endpoint is defined as difference in the cumulative incidence rate of advanced breast cancer during the follow-up period between the intervention and non-intervention groups as previously mentioned. As with the primary endpoints, the sample size was calculated based on the previous study comparing sensitivity between screening with CBE alone and mammography in combination with CBE.

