#### 5.5 Breast density classification

In this study, we used cases enrolled from the screening center in Miyagi prefectures, as we could examine and confirm the breast density. Mammography density measure was evaluated depending on the fifth edition of Breast Imaging Reporting and Data System (BI-RADS), visual judgment data were classified as follows: (a) almost entirely fatty; (b) scattered areas of fibro-glandular density; (c) heterogeneously dense, which may obscure detection of small masses; and (d) extremely dense, which lowers the sensitivity of mammography screening.

Three expert physicians reevaluated mammographic density of the first screening. No personal identifiers were contained in the digital mammograms. All information of screening results, medical check and follow up data were blinded.

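### SAP 7.2.2 compares the arms with an uncorrected robust GEE variance that needs many clusters, and applies it unchanged to the Miyagi density analysis without defining or counting the clusters

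*Combined protocol and SAP*

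**What the plan says.** - **Method.** SAP 7.2.2, for "estimating the primary endpoints in the two groups, GEE taking account of correlations within the cluster will be" the method, continues: "used. For estimation of the parameters, robust variance estimator with a compound symmetry structure as a" working correlation matrix. No bias correction, t or F reference, minimum number of clusters or fallback is given.
- **Level.** SAP 8: "A two-sided test will be performed with a significance level of 5" percent.
- **Data.** SAP 1 makes this the plan for the breast-density analysis. SAP 5.5 restricts the data: "we used cases enrolled from the screening center in Miyagi prefectures, as we could examine and confirm the breast density". SAP 6.1 keeps a comparison of the two arms as objective 1#.
- **Pooling.** SAP 6.2: "Analyses including only subjects who are randomized individually or by cluster will be performed", to see whether the point estimates agree. A randomisation-method-by-arm interaction is then tested in the pooled data, and the two designs are combined if it is not significant. The units in the cluster-randomised part are communities or healthcare providers. Their number is not given.
- **Size of the network.** SAP 2.2: "A total of 42 organizations in 23 prefectures in Japan will participate in the study". This is the only count of sites in the documents.

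**The concern.** The sandwich variance estimates between-cluster variability from the clusters themselves. With few clusters it is biased downward and also noisy, so comparing the Wald statistic with 1.96 rejects too often. The method suits the national data set, but this SAP version applies it to one prefecture without adaptation. A reader cannot tell from the plan whether the Miyagi arm comparison rests on one cluster, a handful, several dozen towns and workplaces, or thousands of individually randomised women.

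Two things are at stake. The first is whether the 5% level is delivered for the arm comparison in Miyagi, or whether a test exists there at all. The second is the pooling decision in SAP 6.2: a variance that is too small makes a false interaction, and hence a refusal to pool, more likely. SAP 6.2 does not say what follows in that case.

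**Working it through.** **1. The plan's own figure.** SAP 2.5 starts from the Miyagi registry study: "Of these, screen-detected breast cancer was in 45 subjects, and interval cancer was in 18 subjects". The sensitivities are 45/63 = 0.714 and 54/63 = 0.857, with mean 0.786. The two-proportion formula gives

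n = [1.960·√(2·0.786·0.214) + 0.842·√(0.714·0.286 + 0.857·0.143)]² / (0.143)² = 128.3,

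so 129 cancers per group, against 130 stated. The conversion 130 × 20,587/63 = 42,481 matches the stated 42,500. The figures reproduce, but the formula is an individual-level one. It contains no cluster number or ICC, so it does not help here.

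**2. The robust variance.** Take a logit model with arm only and independence weights, which equal exchangeable weights when cluster sizes are equal. Cluster j has y_j detected among n_j cancers, and arm a has N_a cancers and sensitivity p_a. For cluster-randomised women the variance of the log odds ratio is the sum over arms of

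Σ_j (y_j − n_j p_a)² / [N_a p_a(1 − p_a)]².

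- *One center as one cluster containing both arms.* The single cluster's summed score is zero at the solution, so the robust variance is exactly zero.
- *g equal clusters per arm (G = 2g in total).* The sum of squares has expectation (g − 1)/g of its target. The statistic then behaves roughly like a t variable on G − 2 df multiplied by √[g/(g − 1)]. The rejection rate is about P(|t| > 1.96·√[(g − 1)/g]). For G = 4 the cut-off is 1.96·√(1/2) = 1.386, and on 2 df the rate is 1 − 1.386/√(1.386² + 2) = 30%. The same formula gives 12% for G = 10, 8% for G = 20 and 6% for G = 40.
- *Individual randomisation with the center as GEE cluster.* The factor is (G − 1)/G on G − 1 df: 40% for 2 centers, 19% for 4, 10% for 10 and 6% for 42.

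**3. Simulation under no arm effect**, 20,000 trials per setting, uncorrected robust z test. The following are assumptions, not in the documents: 120 or 260 cancers at sensitivity 78.6%, or 20,000 women at specificity 90%; beta-binomial outcomes; ICC 0 to 0.05; equal or strongly unequal cluster sizes.

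| Randomised clusters | 120 cancers, ICC 0.01: equal / unequal sizes | Range over all settings |
|---|---|---|
| 4 | 29.2% / 36.3% | 29-44% |
| 6 | 18.1% / 23.4% | 18-29% |
| 10 | 11.1% / 13.8% | 11-18% |
| 20 | 7.1% / 8.7% | 7-12% |
| 40 | 5.3% / 6.4% | 5-9% |
| 80 | 5.2% / 5.5% | 5-7% |

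With individual randomisation and the center as cluster (260 cancers or 20,000 women): 38-43% with 2 centers, 19-21% with 4, 9-11% with 10, about 6% with 42, and no test with 1. With each woman as her own cluster: 4.3-4.9%.

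**4. Check with the SAP's working correlation.** A fitted exchangeable logit GEE (400 trials per setting, 120 cancers, sensitivity 75%, ICC 0.01, cluster-size CV 0.6, Monte Carlo SE about 1 to 2.5 points) gave 43%, 29%, 16%, 12% and 6% for 4, 6, 10, 20 and 42 randomised clusters. A bias-reduced robust variance with t on G − 2 df gave 1.3%, 1.5%, 3.3%, 3.1% and 2.8%.

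**5. Clusters that carry information.** Sensitivity uses only women with cancer. At 63/20,587 there is one cancer per 327 women, so a small community may contribute none. The clusters informing the sensitivity test can therefore be fewer than those randomised.

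**The case against.** The strongest reply is that the size of the problem depends on a number the documents do not give. A reader might infer that the Miyagi test rejects at 2 to 8 times its nominal level. That needs about 2 to 10 clusters, or up to about 20 if sizes are very unequal, and nothing in the documents says Miyagi has so few. Dividing 42 organizations by 23 prefectures (1.8 each) does not show it either, because the units named in SAP 6.2 are communities or providers, and protocol section 3 speaks of towns, villages and workplaces. One organization may cover many of these. At about 40 clusters the inflation is modest, and with each woman as her own cluster there is none. This stands, and it makes the finding conditional.

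Four other tempting inferences also fail:

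- *False rejections in the cluster-only subset.* SAP 6.2 only reviews point estimates there and names no test.
- *An invalid dense versus non-dense comparison.* SAP 7.2.2 assigns GEE to the two arms, not to objective 2#.
- *Wrong confidence intervals for each arm's rates.* SAP 7.2.1 computes these by a binomial method, not from the robust variance.
- *A single center as the extreme of inflation.* A zero variance means the test cannot be computed, which is a different fault. Nor do the documents say that the Miyagi center is one GEE cluster.

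The reply does not remove the gap. Under the reading most favourable to the plan, in which each individually randomised woman is her own cluster, a within-cluster correlation structure has no content for those women, and the SAP would need to say so.

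**Conclusion.** The concern holds in a conditional form. The plan specifies a variance estimator that needs many clusters, applies it to data that may have few or one, and supplies neither the count nor a fallback. The error rate of the Miyagi arm test therefore cannot be determined from the plan. Across the possible readings it runs from nominal (each woman a cluster), through 5-9% at 40 randomised clusters and 11-18% at 10, to 29-44% at 4. With one cluster there is no test. These figures rest on the assumed cancer counts, ICC and cluster sizes set out above, and on a normal reference, since none is named.

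The SAP 6.2 interaction test on pooled data has the same weakness, with false interactions as the result. It cannot be estimated where only one randomisation method is present. This is more than missing detail, because a standard replacement works across the whole range except a single cluster.

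**What to change.** In SAP 7.2.2 and 6.2:

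1. Define the GEE cluster as the unit of randomisation: the community or provider for cluster-randomised women, and the woman herself, with facility as a stratum, for individually randomised women. State the resulting counts for Miyagi and for the cluster-randomised part.
2. Replace the plain robust variance by a Mancl-DeRouen or Kauermann-Carroll corrected one, with a t reference on clusters minus parameters.
3. State that where the Miyagi data come from one center or one randomisation method, the 6.2 interaction test is not run and the arm comparison follows the actual randomisation unit.

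The cost is a few sentences and some programming, with no new data. With 40 clusters the critical value is 2.02 rather than 1.96, so almost nothing is lost. With very few clusters the price is real. At 4 clusters and two parameters the critical value is 4.30, so intervals are at least 4.30/1.96 = 2.2 times as wide; at 6 clusters it is 2.78, at least 1.4 times. The corrected test was also conservative there (about 1% rejection). No correction rescues a single cluster, which is why the definition in item 1 matters most.
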